### Recruitment

All patients satisfying the inclusion and exclusion criteria will be offered recruitment into the trial. Investigators will provide information on possible advantages and disadvantages of the interventions. Patients will be included only after signing written informed consent (*Appendix S1*). To avoid selection bias, screening log of patients excluded from the trial will be kept.

### Randomization

Preoperative randomization will be adopted on the day of admission. A total of 330 subjects will be allocated 1:1 to either the LMH group or the OMH group. The randomization schedule will be generated by the Clinical Trials Centre (CTC) of the principal investigator’s centre, prior to the start of the study. Stratified block randomization (block size of 10) will be used to ensure treatment allocation in equal proportions at each centre. The randomization list will be kept in a set of tamper-evident envelopes. The envelopes will be identical and sealed. The trial identifier with a sequential number will be printed on each envelope. Envelopes will be unsealed to reveal the allocation treatment 1 day prior to surgery.

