## Methods

The Asia-Pacific multicentre randomized trial of laparoscopic *versus* open major hepatectomy for hepatocellular carcinoma (AP-LAPO trial) is an open-labelled randomized trial to be conducted in five Asia-Pacific centres (Department of Surgery, The Chinese University of Hong Kong; Department of Surgery, Kwong Wah Hospital, Hong Kong; Department of Surgery, The First People Hospital of Foshan, China; Department of Biliary Surgery, Eastern Hepatobiliary Surgery Hospital & Institute, Second Military Medical University, China; Department of Surgery, Department of Surgery, West China Medical School of Sichuan University). The trial has been registered at ClinicalTrials.gov of the US National Library of Medicine (NCT04852211). The trial protocol follows the Standard Protocol Items: Recommendations for Interventional Trials (SPIRIT) guideline^13^. The coordinating centre for the trial is the Department of Surgery, The Chinese University of Hong Kong. The trial is free of industrial sponsorship.

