### Blinding

There will be no blinding for all recruited patients, investigators, operating surgeons, and other supporting staff.

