### Statistical plan

The 2-year recurrence-free survival (primary outcome) and overall survival will be evaluated by Kaplan–Meier method and compared by the log rank test. Other secondary outcomes will be compared using the chi-squared test or Fisher’s exact test for categorical variables, and the Mann–Whitney *U* test for continuous variables. *P* < 0.050 will be considered statistically significant. Statistical analysis will be performed using SPSS version 11.0 (SPSS Inc., Chicago, IL, USA).

All clinical data including patients’ demographics, operative details, tumour characteristics, and clinical outcome measure will be collected and centralized at the principal investigator’s centre using a password-protected web-based system to ensure confidentiality of personal information. Continuous clinical data monitoring will be performed by the principal investigator and co-investigators with the help of biostatisticians and research assistants. The data set will be kept confidential until the publication of trial results.

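### One published block size of 10 per centre in an unblinded trial lets anyone who tracks earlier allocations deduce about 15–17% of them with certainty

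*Protocol article*

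**What the plan says.** All references are to the protocol article.

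- **Randomization** fixes a single block size and balances it by centre: "Stratified block randomization (block size of 10) will be used to ensure treatment allocation in equal proportions at each centre". The total and ratio are given as "A total of 330 subjects will be allocated 1:1 to either the LMH group or the OMH group".
- The same section describes the mechanism: "The randomization list will be kept in a set of tamper-evident envelopes". The envelopes are identical and sealed, and "The trial identifier with a sequential number will be printed on each envelope". The Clinical Trials Centre generates the schedule before the study starts.
- On timing, randomization takes place on the day of admission, and "Envelopes will be unsealed to reveal the allocation treatment 1 day prior to surgery". Table 1 (Participant timeline) puts screening and consent at one month before, and allocation at time 0.
- **Blinding**: "There will be no blinding for all recruited patients, investigators, operating surgeons, and other supporting staff".
- **Recruitment** names one measure against selection bias, a log of screened patients who were excluded.
- **Eligibility criteria** require the multidisciplinary team to agree that the tumour suits both approaches.

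The article mentions neither varying block sizes nor withholding the size from sites.

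**The concern.** Sealed envelopes stop someone from reading the next allocation. They do not stop someone from deducing it. Here the three things needed for deduction are all available: the block size is in print, earlier allocations at the centre are visible because nothing is blinded, and the envelopes are used in numbered order. Once one arm has used its five places, the rest of the block is known.

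The timing makes this relevant. If several consented patients are waiting at a centre, the order of admission decides who meets a known allocation. Someone who expected the next place to be laparoscopic could bring forward a patient with a more favourable tumour, or hold one back. Tumour features that make a case easier or harder can also bear on recurrence, so such ordering would act on the primary outcome, 2-year recurrence-free survival. A log of excluded patients would not show it, because every patient involved is included.

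**Working it through.** The plan states no figure for predictability, so there is none to reproduce.

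**Inputs.** Block size 10, hence 5 + 5 at 1:1 (Randomization). Total 330 (Randomization). Five centres (Methods: "is an open-labelled randomized trial to be conducted in five Asia-Pacific centres"). Assumptions: a separate envelope series per centre, which balance at each centre implies but the article does not state outright; and, for one scenario, equal recruitment of 330 / 5 = 66 per centre.

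**Allocations known with certainty.** There are C(10,5) = 252 equally likely blocks. The place after the first k is forced when those k already contain all five of one arm, with probability 2 × C(k,5) / 252:

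| Place | Calculation | Probability forced |
|---|---|---|
| 1st–5th | – | 0 |
| 6th | 2 × 1 / 252 | 0.8% |
| 7th | 2 × 6 / 252 | 4.8% |
| 8th | 2 × 21 / 252 | 16.7% |
| 9th | 2 × 56 / 252 | 44.4% |
| 10th | 2 × 126 / 252 | 100% |

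The sum is 420 / 252 = 1.667 per block. This agrees with the closed form 2m/(m+1) = 10/6 for m = 5.

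- Every centre ends on a complete block: 33 × 1.667 = 55 of 330 (16.7%).
- 66 per centre (six full blocks plus six places): 6 × 1.667 + 0.008 = 10.008; × 5 = 50.0 of 330 (15.2%).
- Uneven centre splits that were tried gave 15.2% to 16.7%.

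**Best-guess rate.** Always guess the arm that is behind, and count ties as one half. The expected number correct per block is m + 2^(2m−1)/C(2m,m) − 0.5. For m = 5 this is 5 + 512/252 − 0.5 = 6.53, or 65.3%. With 66 per centre it is 64.6%.

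**Other fixed sizes, complete blocks.**

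| Block size | Forced | Best guess right |
|---|---|---|
| 4 | 33.3% | 70.8% |
| 6 | 25.0% | 68.3% |
| 8 | 20.0% | 66.6% |
| 10 | 16.7% | 65.3% |
| 12 | 14.3% | 64.3% |

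**Varying sizes.** Simulation with 66 patients per centre, sizes equally likely, and an observer who knows the set of sizes but not their order:

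| Scheme | Certain | Best guess right |
|---|---|---|
| Fixed 10 | 15.2% | 64.6% |
| 8, 10, 12 | about 1.3–1.5% | about 65% |
| 4, 6, 8, 10 | about 1.2% | about 67% |

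The best-guess rates can be checked for complete blocks. For 8, 10 and 12: (5.33 + 6.53 + 7.72) / 30 = 65.3%. For 4, 6, 8 and 10: (2.83 + 4.10 + 5.33 + 6.53) / 28 = 67.1%.

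**The case against.** The design has real safeguards. A Clinical Trials Centre generates the list, the envelopes are tamper-evident, a multidisciplinary team and not one surgeon agrees suitability, all eligible patients are to be offered entry, and exclusions are logged. A block of 10 is also less predictable than a block of 4, 6 or 8. The article is consistent with itself on this point. To exploit a forced place, someone must know all earlier allocations and where blocks start, and must have at least two consented patients whose order can be swapped at that moment. The article gives no information on how often that happens. All of this stands, and it lowers the likelihood of exploitation. None of it prevents deduction from past allocations.

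Four stronger readings are tempting, and the documents do not support them:

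- A reader might infer that the surgeons who schedule cases hold the envelopes at their own centre. The article names neither the scheduler nor the holder, and a condensed article may leave custody to the full protocol.
- A reader might take 55 as a count of biased allocations. It is the upper end of what could be deduced.
- A reader might blame the 65% best-guess rate on the fixed size. Guessing the arm that is behind needs no knowledge of block size, and smaller blocks make that rate worse.
- A reader might conclude that no analysis could deal with such bias. Adjustment for measured prognostic factors can reduce it, and baseline comparisons may help reveal it, but the unmeasured part would remain.

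**Conclusion.** The point holds as a weakness of design that is cheap to improve. The fault is that the block size is fixed and disclosed in an unblinded trial, not that it is 10. Between 15.2% and 16.7% of allocations, about 50 to 55 of 330, can be deduced with certainty by anyone who tracks a centre's allocations. This rests on a separate envelope series per centre, envelopes used in numerical order, and an observer who knows where blocks begin. It measures potential predictability. Nothing in the article shows that bias has occurred or how large it would be. The Statistical plan names a log rank comparison for the primary outcome and describes no adjustment there; adjustment would in any case correct only partly.

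**What to change.** 1. For patients not yet randomised at each centre, have the Clinical Trials Centre issue a new list with block sizes that vary at random and average no less than 10, for example 8, 10 and 12. Do not disclose the sizes to the sites. Certain allocations fall from about 50 to 55 to about 4 or 5 per 330 (0.013 to 0.015 × 330). Leave out blocks of 4 and 6: they would also cut certain allocations, but would raise the best-guess rate to about 67%.
2. The trial already collects its data through a "password-protected web-based system". Where that system allows it, release each allocation only after the patient has been irrevocably registered, so that order cannot be changed once the next allocation can be deduced.

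**Cost.** A new list must be prepared and, for the second step, the web system extended. The largest possible imbalance within a block rises from 5 to 6. A block left unfinished at the changeover could leave a centre up to 5 out of balance. The Trial status section says that recruitment began in December 2021, so the change brings no benefit for patients already randomised, and the size already published cannot be withdrawn.

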### Blinding

There will be no blinding for all recruited patients, investigators, operating surgeons, and other supporting staff.

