## Introduction

Hepatocellular carcinoma (HCC) is the sixth most common malignancy in the world^1^. The practice of screening by ultrasonography and serum *α*-fetoprotein concentration in cirrhotic patients and hepatitis B carriers has led to an increasing incidence of HCC^2^. Curative treatment options for patients with early HCC include hepatic resection, local ablation, and liver transplantation. Hepatectomy remains the mainstay treatment for patients with HCC and non-cirrhotic liver according to European Association for the Study of the Liver (EASL), American Association for the Study of Liver Diseases (AASLD), and ESMO guidelines^3–5^.

Open major hepatectomy (OMH) (resection of greater than or equal to three liver segments) is indicated for large tumours (greater than 5 cm) that are centrally located and/or close to intrahepatic major vessels. OMH is associated with significant morbidity (about 30 per cent), though hospital mortality has been reduced to less than 5 per cent^6^. Wound and pulmonary complications are the most common early complications, but intrahepatic tumour recurrence remains a major problem in up to 50 per cent of patients^7^.

Laparoscopic major hepatectomy (LMH) has become a feasible and effective approach for the surgical management of HCC^8^. LMH seems to be associated with less surgical stress and manipulation of the tumour during surgery^9^, without increasing blood loss, morbidity, and mortality^10^. These potential benefits might lead to long-term survival benefit^11^ and better quality of life for patients. LMH and OMH have been compared in retrospective matching analyses^8,12^. The aim of this multicentre RCT is to compare LMH and OMH for HCC. The primary outcome is recurrence-free survival.

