### Outcomes

#### Primary outcome

The primary outcome is 2-year recurrence-free survival.

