### Follow-up

No adjuvant treatment will be used after surgery. All patients will be followed up every 3–6 months for up to 5 years after operation. Follow-up assessment will include: liver function (clinical assessment of Child’s grade, complete blood count, liver, and coagulation profile); recurrence (based on serum *α*-fetoprotein level, chest X-ray, and CT scan of abdomen with contrast); and quality of life (FACT-G questionnaires).

Patients with intrahepatic recurrence will be managed by laparoscopic re-resection for the LMH group or open re-resection for the OMH group when considered feasible. For patients in whom re-resection is not possible, thermal ablation, transarterial chemoembolization, or salvage liver transplant will be offered according to the decision of the multidisciplinary team.

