### Sample size

Based on a reported 2-year recurrence-free survival rate of 72 per cent after OMH^12^ and an expected 88 per cent after LMH according to a previously reported series^8^, 150 patients need to be recruited to each arm to demonstrate a statistically significant difference with 80 per cent power at the 0.050 level of two-sided significant difference between LMH and OMH^24^. Allowing a 10 per cent dropout rate, 165 patients will be recruited in each arm. This sample size will allow detection of a reduction of 2-year tumour recurrence from 50 per cent in the OMH group to 30 per cent in the LMH group with a similar power and level of significance. Secondary outcomes will be interpreted for hypothesis-generating only.

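### Nobody is masked, including whoever reads the follow-up scans, although recurrence is the main component of the primary outcome and scan reading could be masked at little cost

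*Protocol article*

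**What the plan says.** The Blinding section of the protocol article reads: "There will be no blinding for all recruited patients, investigators, operating surgeons, and other supporting staff". This is an explicit choice, not something a condensed article has left unsaid.

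Under Primary outcome: "The primary outcome is 2-year recurrence-free survival". Under Follow-up, recurrence is based on serum α-fetoprotein together with "chest X-ray, and CT scan of abdomen with contrast". The visit schedule there is "All patients will be followed up every 3–6 months for up to 5 years after operation". Table 1 sets visits every 3 months to month 24 and also lists unscheduled visits.

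No section describes a masked reader, central image review or an endpoint committee. The two external experts under Interim analyses monitor progress and share stopping decisions, and they are not said to judge outcomes. The Discussion states a directional hypothesis, with less recurrence expected after LMH.

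**The concern.** Death needs no interpretation, but recurrence on imaging does: a small or equivocal lesion can be called now, called at the next visit, or not called. Here everyone who might make that call may know the arm, and the trial is built on the expectation that one arm recurs less. If equivocal findings are called later or less often after LMH, the primary comparison moves in the hypothesised direction. Intention-to-treat analysis does not correct this, and neither does a larger sample.

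On the article's own figures recurrence is likely to supply most primary events. For open surgery (OMH) the Introduction says that "intrahepatic tumour recurrence remains a major problem in up to 50 per cent of patients", and that "hospital mortality has been reduced to less than 5 per cent". The article does not spell out the components of RFS, and hospital mortality is not all mortality to 2 years, so this is an inference, though a safe one.

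Two features raise the exposure. Under the Statistical plan, the principal investigator and co-investigators monitor the data continuously. Under Interim analyses, the principal investigator takes part in a stopping decision that depends on the between-arm difference in recurrence. People with a view on the hypothesis may therefore see comparative recurrence while outcomes are still being called.

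**Working it through.** The plan has no figure of its own to reproduce on this point, because no misclassification rate is given. The question is how sensitive the primary test is to a few differently called scans.

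**Inputs from the Sample size section**
- RFS of 72% at 2 years: "Based on a reported 2-year recurrence-free survival rate of 72 per cent after OMH".
- 150 per arm before dropout, two-sided 0.05. The figure of 150 is taken as stated, and the argument does not depend on how it was derived.
- Recurrence of 50%, from the alternative scenario in the same section.

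**Assumptions (not in the article)**
- No true difference between arms.
- A share *m* of LMH recurrences is miscalled, with *m* = 10% or 20%, always in the direction that favours LMH. OMH calls are all correct.

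**Case A: recurrences never called by month 24**

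Expected true events per arm: 150 × 0.28 = 42. Missed in LMH: 42 × 0.10 ≈ 4, or 42 × 0.20 ≈ 8.

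Apparent LMH RFS = 1 − 0.28 × (1 − *m*), which is 74.8% at 10% and 77.6% at 20%.

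Chance of a significant result favouring LMH = Φ[(d − 1.96 × SE₀)/SE₁], where d is the apparent difference, SE₀ the pooled and SE₁ the unpooled standard error.

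- *m* = 10%: d = 0.028. SE₀ = √(2 × 0.734 × 0.266/150) = 0.0510. SE₁ = √((0.72 × 0.28 + 0.748 × 0.252)/150) = 0.0510. Φ[(0.028 − 0.100)/0.0510] = Φ(−1.41) = 7.9%.
- *m* = 20%: d = 0.056, SE₀ = 0.0501, SE₁ = 0.0500. Φ[(0.056 − 0.0983)/0.0500] = Φ(−0.845) = 19.9%.
- With 50% recurrence, the same steps with apparent RFS of 55% and 60% give 13.7% and 41.3%.

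Simulated log-rank tests to month 24 with 3-monthly scans agree: about 8% and 20%, and about 14% and 40–41%.

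**Case B: calls delayed, not lost**

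A delay of one visit removes only those recurrences due to be called at the last visit before the 2-year mark; for the rest it shifts the date. Roughly, 42 events over 8 visits is about 5 per visit. Delaying 10% of them pushes about 0.5 patients past month 24, and 0.5/150 ≈ 0.3 points. Simulation (20,000 trials per scenario, exponential recurrence times, 3-monthly scans, log-rank to month 24) gives the results below.

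**False-positive rate favouring LMH (2.5% with no error)**

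| Assumed error in LMH calls | 72% RFS, 10% / 20% miscalled | 50% recurrence, 10% / 20% miscalled |
|---|---|---|
| One visit (3 months) late | about 3% / 3% | about 3% / 4% |
| Two visits (6 months) late | about 3% / 4–5% | about 4% / 6% |
| Never called by month 24 | about 8% / 20% | about 14% / 41% |

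At 72% RFS the apparent gain in 2-year RFS is about 0.3 to 1.3 points with delay, and 2.8 to 5.6 points when recurrences are never called.

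**The case against.** **The mechanism.** The larger figures need a recurrence to stay uncalled through every later visit to month 24. One arising at month 6 would have to be passed over at six further 3-monthly visits (months 9, 12, 15, 18, 21 and 24). An equivocal reading is more naturally a deferred call, and deferral moves the error rate only slightly. This stands: the never-called figures are an upper illustration, not an expected size.

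**Who reads the scans.** The article never mentions radiologists. That they report the scans follows from the scheduled CT. That they are unmasked follows from the open-label design and the breadth of the Blinding statement. Both are reasonable inferences, but not documented facts, and so is the view that no extra reader is needed.

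**What masking can achieve.** The incisions differ and may leave traces on CT, and a local reader may have access to the patient's record. Visit timing and imaging prompted by α-fetoprotein would remain in unmasked hands. This also stands. It limits the benefit but does not remove it.

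**Readings the article does not support.** A reader might infer that the result will be biased towards LMH; nothing in the article shows the direction or size of any bias. A reader might infer that masked reading was considered and rejected; the article does not discuss it. A reader might also count the absence of a single imaging definition of recurrence as a defect; an article may leave that detail to the full protocol, which is not shown.

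**Conclusion.** The point holds as an avoidable weakness limited to scan reading. The article positively states that no one is masked, the primary outcome rests mainly on interpreted findings, and masking the readers would reduce the exposure at little cost. Open treatment itself is unavoidable and is not criticised.

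The size is uncertain. With 10–20% of LMH recurrences miscalled in one direction, the false-positive rate favouring LMH rises from 2.5% to about 3–5% under delayed calls and about 8–20% if never called (about 3–6% and 14–41% with 50% recurrence). These ranges rest on assumed error rates, error in one arm only, and no true difference. The delayed-call range is the more natural description of equivocal lesions. The never-called range shows how far about 4 to 8 patients could move the result.

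**What to change.** Amend the Blinding section to say that those who report follow-up CT and chest X-ray (presumably each centre's usual radiologist; the article does not name the reader) are not told the allocation or surgical approach on the imaging request.

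For the primary analysis, take the imaging component of recurrence and its date from that report. Keep α-fetoprotein as the Follow-up section has it and apply it identically in both arms, because a CT-only call would narrow the endpoint without saying so. Add a sensitivity analysis that uses the treating team's unmasked call; a difference between the two would show whether masking mattered.

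Cost: protocol text and a small change to request forms at five centres, with no extra scan, no change to sample size and presumably no extra reader. Scans reported before the change stay unmasked unless they are re-read, which would take reader time. Masking will be partial, for the reasons given under the objection, and the report should say so.

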### Statistical plan

The 2-year recurrence-free survival (primary outcome) and overall survival will be evaluated by Kaplan–Meier method and compared by the log rank test. Other secondary outcomes will be compared using the chi-squared test or Fisher’s exact test for categorical variables, and the Mann–Whitney *U* test for continuous variables. *P* < 0.050 will be considered statistically significant. Statistical analysis will be performed using SPSS version 11.0 (SPSS Inc., Chicago, IL, USA).

All clinical data including patients’ demographics, operative details, tumour characteristics, and clinical outcome measure will be collected and centralized at the principal investigator’s centre using a password-protected web-based system to ensure confidentiality of personal information. Continuous clinical data monitoring will be performed by the principal investigator and co-investigators with the help of biostatisticians and research assistants. The data set will be kept confidential until the publication of trial results.

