#### Secondary outcomes

These include 30-day, 90-day, and in-hospital mortality, postoperative complications, quality of life, time to functional recovery, 2-year overall survival, 5-year overall survival, and recurrence-free survival. Surgical stress-related cytokines serum interleukin 6 (IL-6) and immunosuppressive acidic protein (IAP) will be measured before surgery and on postoperative days 1 and 7. Measurement of IL-6 and IAP levels will be performed by immunoassay using commercially available kits (MILLIPLEX^®^ MAP Human Cytokine/Chemokine Magnetic Bead Panel, Merck Ltd, Rahway, NJ, USA).

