### Dissemination plan

The protocol of this trial has been registered in Clinicaltrials.gov. The final report on primary and secondary outcomes will be published upon the completion of 5-year follow-up. Both interim analysis and final analysis will be presented at local and international conferences.

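### The primary log-rank test names neither the centre strata used in randomisation nor a 24-month window, so the comparison of 2-year recurrence-free survival is not fully fixed

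*Protocol article*

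**What the plan says.** All references are to the protocol article.

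- Primary outcome: "The primary outcome is 2-year recurrence-free survival".
- Statistical plan: 2-year RFS and overall survival share one sentence, which says they "will be evaluated by Kaplan–Meier method and compared by the log rank test". No strata, centre term or cut-off time is given.
- Randomization: "Stratified block randomization (block size of 10) will be used to ensure treatment allocation in equal proportions at each centre". The Methods section says the trial is "to be conducted in five Asia-Pacific centres".
- Follow-up: "All patients will be followed up every 3–6 months for up to 5 years after operation".
- Dissemination plan: "The final report on primary and secondary outcomes will be published upon the completion of 5-year follow-up".
- Secondary outcomes include "2-year overall survival, 5-year overall survival, and recurrence-free survival", where RFS carries no time limit of its own.
- Sample size: two scenarios, both at 2 years. One is RFS of 72% after open and 88% after laparoscopic surgery. The other is recurrence of 50% and 30%.

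**The concern.** Two features of the design do not reach the stated test.

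The first is the time window. A log-rank test compares whole curves over the follow-up it is given. The endpoint and the sample size are set at 24 months, but data will exist to 60 months when the final report is written. If the test used all of them, nothing would separate the primary RFS comparison from the secondary one, and its P value could reflect differences that arise only after year 2. The trial is unblinded, the investigators monitor the data continuously, and interim results will be presented at conferences. The window should therefore be fixed in writing before results are known.

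The second is centre. Blocking within centre balances the arms on centre. An unstratified test ignores that balance in its variance, so if centres differ in recurrence risk the test is conservative and gives up some power.

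**Working it through.** **The plan's own figure.** For 72% v 88%, two-sided 0.05 and 80% power, the pooled-variance formula n = [1.96·√(2·0.80·0.20) + 0.8416·√(0.72·0.28 + 0.88·0.12)]² / 0.16² gives 97 per arm (110 with continuity correction), not 150. With HR = ln 0.88 / ln 0.72 = 0.389, Schoenfeld's formula gives 36 events, or 36/0.40 = 90 per arm. At 150 per arm the power is about 94% (two proportions) or 95.5% (Schoenfeld, 60 events). That discrepancy is a separate matter; here it explains why the powers below sit near 95%.

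**Share of events after month 24.** Assumptions: constant hazard in each arm, 150 per arm, no loss to follow-up. Survival at 60 months is the 24-month value to the power 60/24 = 2.5.

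- 72% v 88%: by month 24, 150 × (0.28 + 0.12) = 60 events. By month 60, 150 × [(1 − 0.72^2.5) + (1 − 0.88^2.5)] = 150 × (0.560 + 0.274) = 125. Share after month 24: 65/125 = 52%.
- 50% v 30% recurrence: by month 24, 150 × (0.50 + 0.30) = 120. By month 60, 150 × [(1 − 0.5^2.5) + (1 − 0.7^2.5)] = 150 × (0.823 + 0.590) = 212. Share: 92/212 = 43%.

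**Simulation.** From the plan: 165 per arm, five centres, 1:1 within centre, 72% v 88% at 24 months. Assumed, because the documents give no figure: equal-sized centres, piecewise-constant hazards, 10% loss per 24 months, 60 months of follow-up for everyone, and a between-centre SD of the log hazard of 0, 0.3 or 0.6. The five centres sit at −1.414, −0.707, 0, 0.707 and 1.414 SD, so an SD of 0.6 is a ratio of exp(0.6 × 2.828) = 5.5 between the highest- and lowest-risk centres; an SD of 0.3 is 2.3. There were 3,000 trials per cell. The Monte Carlo standard error is √(0.05 × 0.95/3000) = 0.4 points near 5% or 95%.

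Percentage of trials with P < 0.05, at centre SD 0 / 0.3 / 0.6:

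| Truth | All follow-up, unstratified | All follow-up, stratified | Cut at 24 months, unstratified | Cut at 24 months, stratified | Kaplan–Meier difference at 24 months |
|---|---|---|---|---|---|
| No effect | 4.9 / 4.9 / 2.6 | 4.9 / 5.1 / 4.9 | 4.8 / 5.9 / 3.9 | 4.7 / 6.0 / 5.0 | 5.2 / 5.6 / 4.3 |
| Proportional hazards, HR 0.389 | 99.9 / 99.9 / 100.0 | 99.8 / 99.9 / 100.0 | 95.0 / 95.3 / 95.9 | 95.0 / 95.5 / 96.6 | 95.6 / 95.2 / 95.8 |
| HR 0.389 to month 24, then equal hazards | 63.9 / 64.7 / 61.1 | 63.9 / 67.7 / 72.7 | 94.7 / 95.6 / 96.9 | 94.8 / 95.9 / 97.1 | 94.8 / 95.5 / 96.5 |
| HR 0.389 to month 24, then HR 1.5 | 9.8 / 8.8 / 9.2 | 9.9 / 10.8 / 17.4 | 95.0 / 96.0 / 96.3 | 94.9 / 96.2 / 97.1 | 94.9 / 96.0 / 95.9 |
| No difference to month 24, then HR 0.5 | 39.9 / 36.6 / 30.3 | 39.3 / 37.0 / 34.0 | 4.3 / 4.4 / 3.7 | 4.4 / 4.5 / 4.5 | 4.7 / 4.6 / 4.3 |

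**Reading the window.** Compare the first and third result columns. Cut and uncut tests separate widely once hazards are not proportional: 61–65% against 95–97% if the benefit stops at month 24, and 30–40% against about 4% if it starts only then. Under proportional hazards the uncut test is the more powerful.

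**Reading centre.** For the 24-month test at the design effect, stratifying gains 0, 0.2 and 0.7 points. The largest gain is 72.7 − 61.1 = 11.6 points; it needs SD 0.6, all follow-up and hazards that become equal after month 24. Type I error of the unstratified uncut test falls to 2.6% at SD 0.6.

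**A weaker effect.** Powers near 95% leave little room for a gain to show. With HR 0.50 (not the plan's value), 150 per arm and 24 months, 6,000 trials per cell gave unstratified against stratified power of 79.5% v 80.9% at SD 0.45 and 80.7% v 84.1% at SD 0.72.

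**The case against.** The article does not say that the test is unstratified or that it uses all follow-up. Strata and censoring dates are often left to a statistical analysis plan, which may exist and is not shown. The sentence in the Statistical plan has 2-year RFS as its subject, so a comparison limited to 24 months is a natural reading. The separate listing of RFS as a secondary outcome supports it. The Dissemination plan fixes when results are published, not which data the primary test uses. All of this stands, and it makes the point a request to fix wording.

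The numerical objections also stand. The centre gain depends on differences between centres for which the documents give no figure, and at the design effect it is negligible for a 24-month test. The disagreement between cut and uncut tests depends on assumed non-proportional hazards. A log-rank test censored at 24 months still compares curves over 0–24 months; only the Kaplan–Meier difference at 24 months addresses the 2-year rate itself.

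What does not follow is that the point can be dropped. The article names the primary test, the wording admits two readings, and the two can give different answers.

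**Conclusion.** The point holds as an inexpensive improvement. The stated primary test does not carry the centre strata of the randomisation and does not fix its window at the 2-year endpoint. The window matters more. Under constant hazards and no loss to follow-up, 43% to 52% of the events in an uncut test would fall after month 24, and its result can depart from the 2-year comparison if the treatment effect changes over time. Centre is the smaller part: no loss if centres do not differ, under 1 point for the 24-month test at the design effect, and more only with strong centre differences and longer follow-up.

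A reader might infer four stronger things that the documents do not support:

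- That the plan definitely fails to test 2-year RFS. The wording allows a 24-month reading.
- That omitting the cut-off costs precision. Under proportional hazards the uncut test has about 99.9% power against 95%.
- That omitting centre inflates false positives. With strong centre differences the unstratified test errs in the conservative direction.
- That an uncut P value would rest mostly on late events. This fails on the plan's second scenario, where the share is 43%.

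**What to change.** In the Statistical plan, state that the primary test is a log-rank test stratified by centre, with RFS follow-up censored at 24 months. Report the Kaplan–Meier difference in 2-year RFS with its 95% CI as the direct estimate of the 2-year endpoint. Keep RFS over longer follow-up as a secondary outcome. If an analysis plan already says this, bring the protocol wording into line. A Cox model adjusted for baseline prognostic factors is an optional extra and is not needed to close this point.

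The change is to wording only: no added data or patients, and standard software does it. The one statistical cost is that, if hazards stay proportional to 5 years, the 24-month cut uses fewer events (about 95% power against 99.9% at the design effect). Stratifying costs nothing visible when centres do not differ (95.0% either way for the 24-month test, with equal-sized centres).
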